### Intervention

2.9

#### Study schedule

2.9.1

The study schedule is presented in Table 1. At the screening visit, participants will sign the informed consent form. In a baseline questionnaire, the following information will be obtained: age, occupation (physical/nonphysical), education level, last menstrual period, previous use of acupuncture, and expectation to acupoint thread embedding treatment. Moreover, Short-Form of McGill Pain Questionnaire (SF-MPQ), Osteoporosis Symptom Score, Osteoporosis Quality of Life Scale (OQOLS), 16-item Assessment of Health-Related Quality of Life in Osteoporosis (ECOS-16) must be completed at the baseline (week 0). Thereafter, study subjects will be randomized. There is a 3-month study period and a 1-month follow-up period for each group. In the study period, SF-MPQ, OQOLS, ECOS-16, and Osteoporosis Symptom Score will be evaluated every 4 weeks. fMRI and bone density test will be tested 2 times: in week 0 and week 12.

**Table 1 T1:**
[figure not shown]
Trial flow and time schedule: enrollment, interventions and assessments.

#### Treatment group intervention

2.9.2

Acupoint thread embedding treatment will be applied to patients in the treatment group fortnightly, a total of 6 times during 3 months. Main acupoints are BL23, SP6, and RN4. If it is a liver-kidney deficiency case, BL18, GB39, BL11 will be added. If it is a kidney yang deficiency case, BL20, ST36 will be added. In each treatment, RN4 is a required acupoint. The rest acupoints can be used in the alternation of the left/right side. The location method is according to *Location of Acupoints* the National Standards of P.R promulgated by the State Bureau of Technology Supervision. The operating method follows the National Standards of P.R (GB/T 21709.10-2008) manipulations of acupuncture and moxibustion—Part 10 Acupoint catgut embedding. Details about the intervention group interventions and the acupoints location are described in the Standards for Reporting Interventions in Clinical Trials of Acupuncture (STRICTE) checklist in Tables 2 and 3.^[12]^

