**Methods::**

This parallel designed, exploratory randomized, controlled, assessor-statistician-blinded, positive medicine clinical trial will include 70 participants with PMOP recruited from 2 traditional Chinese Medicine hospitals. These participants will be randomly allocated to a treatment group (Group Embedding) and a control group (Group Medication) in a 1:1 ratio. Participants in the treatment group will receive acupoint thread embedding treatment once 2 weeks in the following predefined acupoints: Shenshu (BL23), Sanyinjiao (SP6), Guanyuan (RN4), Ganshu (BL18), Dazhu (BL11), Xuanzhong (GB39), Zusanli (ST36), and Pishu (BL20). Meanwhile, the participants in the control group will take 0.3 mg Climen tablet orally, 1 tablet/day; every month has a schedule of the 21-day-continuous-taking-medicine period, and 7-day tablet-free period. There is a study period of 3 months and a follow-up period of 1 month for each group. The primary outcomes will be the following therapeutic indexed: Short-Form of McGill Pain Questionnaire (SF-MPQ), Osteoporosis Symptom Score during the observation period and follow-up period. The secondary outcomes will be Osteoporosis Quality of Life Scale (OQOLS), 16-item Assessment of Health-Related Quality of Life in Osteoporosis. In addition, functional magnetic resonance imaging (fMRI) scans and bone density test will be done before and after the observation period to show cranial neuroimaging changes. All the outcomes will be evaluated before and after treatment. The safety of interventions will be assessed at every visit.

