### Eligibility criteria: inclusion criteria

2.4

(1)Female subjects aged 45 to 70 years and have natural menopause for more than 2 years;(2)After the dual-energy X-ray absorptiometry, *T* value -2.5 ∼ -5.0 (L2-L4), and meet the diagnostic criteria of TCM syndrome;(3)Subjects voluntarily participated in the study and signed informed consent;(4)Subjects who can be able to cooperate and complete the fMRI scan.

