### Randomization and allocation concealment

2.7

The randomization number will be generated by PEMS 3.1 and made into random cards. The randomization number will be sealed in a predetermined randomization opaque envelope. The patients’ screening sequence numbers will be printed on the outside of the envelope, whereas the group names will be printed inside. The envelope containing an allocation sequence number for each patient will be opened right after each patient is verified to meet the eligibility criteria and has signed the written informed consent form. If any error or disclosure regarding randomization occurs, a new randomization sequence will be generated from the problematic serial number and applied to subsequent patients.

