### Statistical analysis

2.14

Image data processing includes using methods such as independent component analysis (ICA) and function binding, applying professional software such as MRIcro for windows, Xjview 8.1, SPM 12, and Matlab 5.1.

Statistical analysis technique is used to apply a statistical test to the difference of prior-treatment and posttreatment, and to examine the curative effect difference within groups and among groups of all curative effect indexes. We will adopt the 2-sided test for all statistical tests. It is considered that the tested differences are statistically significant if *P* value is less than or equal to .05. If *P* value is greater than or equal to .05, the tested differences are not statistically significant. Details are as following.

Measurement data includes the *t* test will be adopted to run comparison among groups. When it does not comply with the normal distribution, we will choose Wilcoxon rank-sum test. Similarly, we will run paired *t* test toward the difference of prior-treatment and post-treatment, and it will be changed into Wilcoxon rank-sum test, while it does not comply with the normal distribution.

Enumeration data: We will use the Chi-square test, calibration Chi-square test, and Fisher exact method to run comparison among groups.

Ranked data: Wilcoxon rank-sum test will be applied to run comparison among groups and signed rank-sum test to run comparison within groups.

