## Discussion

3

This study is a randomized, controlled, assessor-statistician-blinded, positive medicine clinical trial, funded by the National Natural Science Foundation of China. The purpose of this project is to verify the efficacy and safety of acupoint thread embedding on PMOP. The goal is hoped can be achieved by evaluating BMD measurement, fMRI, clinical integral scale, etc. This study is based on syndrome differentiation of viscera (kidney syndrome differentiation) to determine the acupoints used in thread embedding therapy. The researchers searched papers for nearly 10 years and found that the treatment of osteoporosis based on viscera syndrome differentiation (kidney syndrome differentiation) is effective. It has been investigated that many cases of osteoporosis patients in Nanjing responded to the treatment of “ tonifying kidney and benefiting marrow” method. In the treatment of osteoporosis, the method has achieved good evaluation.^[13]^ In TCM theory, “kidney controls bones and marrow moistens bones,” which means that the kidney essence can improve the growth and development of human, and bone formation. Broadly speaking, the kidney essence consists of marrow, spinal cord, and brain. And the brain is the “marrow sea”; it plays a leading role in the growth and development of bone. The kidney affects the growth and development of bone by its close connection with the brain. Combining with the theory of “brain-bone mass regulation” in modern medicine,^[14]^ the researchers believe that the method of “tonifying kidney and benefiting marrow” affects kidney and brain, then influences bone metabolism, and is a symptomatic treatment for osteoporosis.

Furthermore, the previous study found that acupoint stimulation has certain effect on perimenopausal syndrome.^[9]^ Therefore, the study is designed by thread embedding therapy at acupoints after syndrome differentiation, in order to provide evidence for the clinical efficacy and the effect of the brain-bone mass regulation mechanism in the nervous center.

In addition to using SF-MPQ, OQOLS, ECOS-16, and osteoporosis symptom scores to evaluate clinical efficacy, the study also chose BMD measurement and MRI scan to provide clear, effective, and visible evidence to verify the efficacy and safety of acupoint thread embedding on PMOP.

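### The embedding prescription depends on TCM syndrome type, but the stated between-group tests use neither type nor hospital: a small loss of precision and exposure to chance imbalance that adjustment would remove cheaply

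*Protocol article*

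**What the plan says.** Section 2.9.2 gives every woman in the embedding arm a common core: "Main acupoints are BL23, SP6, and RN4". It then branches on syndrome type: "If it is a liver-kidney deficiency case, BL18, GB39, BL11 will be added" and "If it is a kidney yang deficiency case, BL20, ST36 will be added". The Discussion presents this branching as the principle of the design: "This study is based on syndrome differentiation of viscera (kidney syndrome differentiation) to determine the acupoints used in thread embedding therapy". Control treatment (Section 2.9.3) does not depend on type.

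Women in both arms must "meet the diagnostic criteria of TCM syndrome" to enter (Section 2.4). The baseline questionnaire items listed in Section 2.9.1 do not include syndrome type.

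On allocation, Section 2.7 says "The randomization number will be generated by PEMS 3.1 and made into random cards" and describes sealed envelopes. It mentions no strata. Patients are "recruited from 2 traditional Chinese Medicine hospitals" (Abstract).

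On analysis, Section 2.14 states that for continuous data the t "test will be adopted to run comparison among groups", with the Wilcoxon rank-sum test if the data are not normal. No covariate or stratum is named.

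**The concern.** Syndrome type is a pre-randomisation characteristic that decides which points an embedding patient receives. If type also relates to pain or symptom scores, a test that ignores it carries the between-type variation as noise. In a trial of 70, the arms can also differ noticeably in type by chance. Hospital is a second known factor, and the test ignores it too.

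There is a practical side. Type is needed for treatment only in the embedding arm. If it were recorded only when points are chosen, type would not be comparable between arms, and neither adjustment nor a within-type description could be recovered later.

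There is also a reporting side. The Abstract lists eight predefined points for the embedding group, whereas Section 2.9.2 gives six for one type (three core plus three) and five for the other (three core plus two). These passages should be reconciled, because the Abstract reads as one regimen and the body describes a tailored one.

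**Working it through.** **Inputs from the article.** 35 women per arm, 1:1 (Section 2.2); two-sided tests at .05, t or rank-sum, no covariates (Section 2.14). No effect size, SD or power is given for the sample size of 70, so the only plan figure that can be reproduced is 35 + 35 = 70. For scale, 35 per arm gives 80% power for a difference of 0.67 SD.

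**Assumptions, not in the article.** Share of one type π = 30% to 50%. Shift in outcome between types γ = 0 to 1.0 SD. Within-type SD = 1. Randomisation unstratified.

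**1. Chance imbalance.** Let K of the 70 women have one type, and let X of them fall in the embedding arm. Then X is hypergeometric (70, K, 35), and the gap in type share is (2X − K)/35. A gap of at least 0.20 in one direction needs X ≥ (K + 7)/2.

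- π = 50%: K = 35, X ≥ 21. Doubling for both directions gives probability 0.151. SD of the gap is 12.0 points.
- π = 30%: K = 21, X ≥ 14. Probability 0.117. SD of the gap is 11.0 points.
- With π = 20% (K = 14) the probability falls to 0.034.

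**2. Is the comparison biased?** In simulation (20,000 runs per scenario, unadjusted t test), the mean estimate was −0.003 to 0.001 at a true effect of 0, 0.497 to 0.503 at 0.5, and 0.667 to 0.672 at 0.67. Type I error was 0.047 to 0.053, including at γ = 1.0 SD. There is no bias over randomisations.

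**3. Loss of precision.** The standard error within type is √(2/35) = 0.239. Ignoring type gives approximately √[(2/35)(1 + γ²π(1 − π) × 70/69)]:

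- γ = 0.5: 0.245 to 0.247
- γ = 1.0: 0.263 to 0.268

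The simulated values agree (0.245 to 0.250 and 0.264 to 0.269).

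**4. Shift given an unlucky draw.** When the gap is at least 20 points in one direction, its exact mean is 0.222 (π = 30%) or 0.229 (π = 50%). The shift is γ times this:

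- γ = 0.5: 0.11 SD (simulation 0.11 to 0.13). Conditional type I error is about 0.07.
- γ = 1.0: 0.22 to 0.23 SD. Conditional type I error is about 0.12.

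**5. What adjustment for type buys.** Simulated power at a true effect of 0.67 SD, with the range covering π = 30% and 50%:

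| γ (SD) | Unadjusted | Adjusted | Gain, points |
|---|---|---|---|
| 0 | 0.785–0.793 | 0.778–0.787 | −0.6 |
| 0.3 | 0.780–0.784 | 0.784–0.786 | 0.2–0.4 |
| 0.5 | 0.764–0.771 | 0.782–0.784 | 1.4–1.8 |
| 0.8 | 0.726–0.734 | 0.779–0.784 | 4.5–5.8 |
| 1.0 | 0.695–0.707 | 0.779–0.783 | 7.2–8.8 |

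Type I error with adjustment was 0.046 to 0.053. Hospital was not simulated. A two-level hospital factor with a similar effect would behave in the same way.

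**The case against.** The strongest reply is that a randomised trial needs no adjustment to be valid. That stands. A reader might infer that chance imbalance in type biases the comparison, but step 2 shows that it does not: the t test's standard error already contains the between-type variance, and an unlucky draw can fall in either direction.

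A reader might also infer that pooling two prescriptions is an error. The article does not support this. It defines the intervention as embedding with points chosen by syndrome differentiation, both types share a core, and nowhere does it promise to credit the effect to a point set. The tailored strategy against Climen is a legitimate estimand.

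The size of the gain is assumption-driven. The article does not describe the syndrome criteria or say how strongly type relates to outcome. If groups are compared on change from baseline, a stable level difference between types would largely cancel. This stands, and it keeps the point small.

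The article is condensed. Strata may be set elsewhere, and the schedule and acupoint tables are not shown, so the silence in Section 2.7 and on when type is recorded is weak evidence. The test in Section 2.14, however, is stated and not left open, and it is the part being questioned.

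Finally, a hospital main effect does not deal with operator variation confined to the embedding arm. That is correct. Hospital is proposed only as a known source of outcome variation.

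**Conclusion.** The point holds as a minor matter of efficiency and interpretation in a trial that the article calls exploratory. The stated tests ignore a pre-randomisation factor that determines the active prescription, and they ignore the known hospital factor. The comparison remains valid.

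The exposure is a 12 to 15% chance of a type gap of 20 points or more, if one type makes up 30 to 50% of patients and randomisation is unstratified. With a 0.5 SD type effect, such a gap moves the estimate by about half of its standard error or a little less (0.11 to 0.13 against 0.24 SD). Adjustment is worth about 0 to 2 points of power for a weak to moderate type effect and 5 to 9 for a strong one. If type has no effect, it costs about half a point. Which case applies cannot be told from the article.

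**What to change.** - Record syndrome type on the CRF for every woman, in both arms, before her envelope is opened, or confirm that this is already done.
- In Section 2.14, replace the two-sample t test by a linear model with treatment, syndrome type and hospital as fixed factors. For clearly non-normal scores, use a rank-based test stratified by the same factors, so that the rank option is kept.
- Describe the pooled result as the effect of the syndrome-tailored embedding strategy against Climen, and reconcile the Abstract's list of points with Section 2.9.2.
- Give the treatment difference within each type with a 95% CI, as description only. At a 50:50 split there are about 17.5 women per arm per type, so the interval is about ±1.96 × √(2/17.5) = ±0.66 SD, too wide to separate the two prescriptions.

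The cost is one CRF field, a sentence or two of analysis wording and about two degrees of freedom, with no extra patients or visits. No change to the envelopes is needed. Recruitment began in 2018, and in the simulation stratifying without adjusting only made the t test conservative (type I error 0.043 at a 0.5 SD type effect and 0.031 at 1.0 SD).

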**Table 2 T2:**
[figure not shown]
Acupoints selects.

#### Control group

2.9.3

The participants in the control group will be prescribed oral administration of Climen (2 mg Estradiol 17β-valerate and 1 mg Cyproterone 17α-acetate) tablets (1 tablet 30 minutes before sleep once per day for 21days and then stop medicine for a week; lasting for 12 weeks). The Climen tablets are produced by Schering GmbH Und Co. ProduktinosKG (Guangzhou, China) (Approval No. J20130006).

#### Adverse events

2.9.4

During the research, some adverse reactions may occur. Researchers will monitor every patient with adverse reaction.

The following adverse reactions may happen after the acupoint thread embedding:

(1)Local reaction: mostly some sterile inflammation with inflamed hot pain within 5 days. Some cases may be more severe, like a small amount of milky-white exudation at the embedding spot caused by fat liquefaction because of thread stimulation. Circumstances above should not require any special treatment.(2)General reaction: some patients may experience temperature rising after the treatment 4 to 24 hours, which mostly around 38°C. It will fade away in 2 to 4 days by itself. Usually, hemogram of each patient may rise in different levels, and it will return to normal in 3 to 5 days.

If adverse reactions occur, the following treatment will be used.

(1)Pain at implantation acupoint: Apply hot compress.(2)Local swelling, progressive pain, and fever 3 to 4 days after the implantation: Lack of strict asepsis and inappropriate protection of the wound could cause secondary infection, which mostly occurs some inflammatory symptoms. Apply hot compress and anti-infective treatment would help.(3)Nerve injury: It is usually caused by incorrect operation or excessive stimulation or carelessness, and can be avoided with the careful operation.(4)Hemorrhage: It is usually caused by the puncture on the vessels or excessive stimulation, in which case pressure dressing on the puncture point would stop the bleeding.(5)Thread allergy: local itching or swelling or fever can be remitted by antianaphylaxis treatment.

Climen, which includes estradiol and cyproterone acetate, is one of the estrogen and progestogen/anti-androgen (HRT). It is used in HRT for women with an intact uterus, used to substitute for a lack of estrogen production by the ovaries during menopause. It helps prevent postmenopausal bone loss (osteoporosis) and reduce risk of fracture. The most commonly reported side effects when taking Climen include breast tenderness, breast pain, abdominal pain, nausea, edema, headache, depression, changes in body weight, and changes in libido.

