### Safety assessment

2.13

At every visit, the physical examination will be performed, and adverse events will be checked. Blood samples will be collected at week 0 and week 12. Blood routine test, liver function (alanine aminotransferase), and kidney function (serum creatinine) will be done at the beginning and the end of the intervention period.

Possible adverse events due to acupoint thread embedding include allergy, local infections, subcutaneous hematoma, and so forth. Any adverse events or reactions that occur during the study process will be addressed properly and analyzed by the investigator. Serious adverse events associated with the trial should be reported to the principal investigator immediately. All unexpected and unintended responses will be documented as adverse events by the researcher at every visit, even if they are not necessarily related to the acupuncture intervention. The details of adverse events will be carefully recorded in the CRF by the corresponding research staff.

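### Dated embedding reactions fall within about 5 days of a session, but no embedding-arm contact is stated before day 14, while controls are seen weekly and contacted daily

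*Protocol article*

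**What the plan says.** Section 2.9.4 of the protocol article dates four things after embedding:

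- Local reaction: "Local reaction: mostly some sterile inflammation with inflamed hot pain within 5 days".
- Fever, starting 4 to 24 hours after the session: "It will fade away in 2 to 4 days by itself".
- Blood count: "hemogram of each patient may rise in different levels, and it will return to normal in 3 to 5 days".
- A picture linked to secondary infection, for which anti-infective treatment is foreseen: "Local swelling, progressive pain, and fever 3 to 4 days after the implantation".

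Nerve injury, hemorrhage and thread allergy are listed without a date and are outside this point.

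Section 2.13 ties detection to visits: "At every visit, the physical examination will be performed, and adverse events will be checked", and "All unexpected and unintended responses will be documented as adverse events by the researcher at every visit". For the embedding arm the text gives two kinds of contact. Section 2.9.2 says "Acupoint thread embedding treatment will be applied to patients in the treatment group fortnightly, a total of 6 times during 3 months". Section 2.9.1 sets the common assessments, for example "Osteoporosis Symptom Score will be evaluated every 4 weeks". Table 1, the visit schedule, is not shown.

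For the control arm, section 2.15 adds a weekly face-to-face interview at which one week of Climen is handed out, and daily contact by call, WeChat or message about taking it. No similar contact is stated for the embedding arm.

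**The concern.** The reactions with a stated date are short-lived, and the stated contacts are two weeks apart. If adverse events are looked for at visits, a reaction that begins and ends in the first week after a session is recorded only if the participant volunteers it or remembers it at the next session. A suspected infection that starts on day 3 or 4 reaches the researchers promptly only if the participant calls in.

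The control arm is placed differently. Its weekly interviews and daily messages exist to secure compliance, but each is an occasion on which a side effect can be mentioned. Safety of embedding is part of the objective in section 2.1. A lower adverse-event count under embedding could therefore partly reflect fewer occasions to report. Events that were never collected cannot be recovered by a later analysis.

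**Working it through.** The plan gives no figure to reproduce. The check lays out the stated contacts by day and measures the distance from each dated reaction to the next one.

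**Embedding arm, first session assumed at week 0**
- Six fortnightly sessions (2.9.2): days 0, 14, 28, 42, 56, 70.
- Four-weekly assessments (2.9.1): days 0, 28, 56, 84.
- Combined: days 0, 14, 28, 42, 56, 70, 84. Day 0 cannot detect an event after treatment, so 6 contacts count, and none falls on days 1–13 after a session.

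**Distance from dated reaction to next stated contact (2.9.4)**
- Local reaction, window ends day 5: 14 − 5 = 9 days.
- Fever ends between 4 h + 2 d = 2.2 d and 24 h + 4 d = 5.0 d, so at least 14 − 5 = 9 days.
- Blood count normal by day 5: 9 days. If counted from 24 hours, normal by 1 + 5 = day 6: 8 days.
- Suspected infection, onset day 3 or 4: 14 − 3 = 11 or 14 − 4 = 10 days.

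**Control arm, face to face (2.9.3 and 2.15)**
- Interviews in tablet weeks only: 3 cycles × 3 weeks = 9 (days 0, 7, 14, 28, 35, 42, 56, 63, 70). Adding day 84 and removing day 0 gives 9 + 1 − 1 = 9.
- Interviews in all 12 weeks (days 0, 7, …, 77): 12 + 1 − 1 = 12.
- The assessments on days 28 and 56 coincide with interviews and add nothing.

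**Ratio of post-baseline face-to-face contacts to day 84:** 9/6 = 1.5 to 12/6 = 2.0. Daily remote contact comes on top, on 3 × 21 = 63 days if limited to tablet days or 12 × 7 = 84 days if not.

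**If the first session is later than week 0.** Suppose it falls d days after week 0, with d from 1 to 13. The day-28 assessment then comes 28 − (d + 14) = 14 − d days after session 2, and the same holds for sessions 4 and 6. Sessions 1, 3 and 5 still have no contact on days 1–13. The embedding arm then has 5 later sessions + 3 assessments = 8 contacts after its first treatment. With the control count held, the ratio is 9/8 = 1.1 to 12/8 = 1.5.

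**The case against.** The strongest reply is that this argues from silence in a condensed article whose schedule table is missing. Interim calls, diaries or instructions to phone in may exist in the full protocol. In part this stands: any such contact would narrow the gap. But the article itself states the reaction times, the visit-based rule and both contact schedules, and the inequality follows from those.

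Second, no unequal collection rule is stated. Section 2.13 applies to both arms, the contacts in 2.15 concern medication, and the text does not say that the weekly interview counts as a visit. This stands. A reader might infer that controls are actively asked about adverse events more often; the document supports only a greater opportunity to report.

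Third, a reader might infer that embedding infections would go undetected. The text does not support that. Swelling, progressive pain and fever are symptoms a participant is likely to report, a persisting infection could still be seen on day 14, and 2.9.4 promises monitoring once a reaction is known. That promise sets no contact for finding one, so late or incomplete recording remains the likely effect.

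Fourth, a reader might take the Discussion's remark that embedding patients may have more contact as contradicted by the schedule. It is not. The remark concerns contact with acupuncturists and its influence on therapeutic effect. It does not address safety reporting, so it neither creates nor corrects this problem.

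Finally, section 2.14 names no between-arm test for adverse events. The harm therefore lies in any comparison of safety, formal or descriptive, that the stated objective invites.

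**Conclusion.** The point holds as unequal opportunity to report. On the stated schedule, embedding participants have no contact on days 1–13 after a session, so the dated reactions depend on self-report or on recall 9 to 11 days later. Controls have 1.5 to 2.0 times as many post-baseline face-to-face contacts, before remote contact. The likely direction is under-recording of short-lived embedding reactions, which would favour embedding. The size of any resulting bias in event counts cannot be derived from the document.

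This rests on three assumptions: the first session is at week 0, Table 1 holds no further embedding visits, and no interim contact is specified elsewhere. A later first session would lower the ratio but leave sessions 1, 3 and 5 uncovered. The efficacy outcomes are not affected. This is an inexpensive improvement to safety collection and participant care.

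**What to change.** In section 2.13, add a short scripted adverse-event check by phone or WeChat on day 3 or 4 after each embedding session: study days 3–4, 17–18, 31–32, 45–46, 59–60 and 73–74. The script covers both embedding reactions and Climen side effects since the previous check. Existing staff other than the blinded assessor and data collector make the contact. Ask controls the same questions on the same study days within the daily contacts already planned.

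Compare the arms on adverse events collected at all contacts common to both: these six checks, the 4-weekly assessments including week 12, and follow-up. Also report all adverse events from any source, flagging those found at arm-specific contacts such as embedding sessions or weekly Climen interviews. The comparison should not be limited to the six checks. They end on day 73–74 and would drop later events and those found on examination.

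The cost is up to 35 × 6 = 210 short calls in the embedding arm and a few sentences in 2.13. Controls need up to 210 question sets but no new contacts. With Climen started on day 0, tablet days are 0–20, 28–48 and 56–76, and all six check days fall within them; the same holds for a start on day 1, 2 or 3.

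Two gaps remain. A call cannot capture the blood-count rise. A reaction that first appears on day 5 is picked up at the next contact, by recall.
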